### Data collection and checking

An online case-report form is used for the collection of data. Blinded and patient identifiable data are stored separately in secure databases. The investigation center stores all identifiable patient data. Research assistants from the promoting center work closely with local investigators to obtain data as complete and accurate as possible.

### Study monitoring

The sponsor (Nantes University Hospital) is in charge of data monitoring. Site staff will be available to facilitate the monitoring visits and ensure that all required documentation is available for review. Study initiation visits have been carried out at all sites before recruitment begins at that site. During regular monitoring visits realized throughout the trial, an independent research assistant will carry out Source Data Verification of trial data, verify informed consent forms, and ensure the Investigator Site Files’ completeness.

### Study oversight

Study sponsor is the Nantes University Hospital ([name], [contact]). Experienced research staff monitored the study for quality the integrity of data in all the participating centers. Serious adverse events and unexpected related or possibly related severe events are reported to the sponsor within 7 days.

The sponsor appoints an independent data and safety monitoring board (DSMB). The DSMB is composed up of 3 people with no connection to the research, including one co-author of the French Guidelines on muscle relaxants and reversal in anesthesia [20], one pharmacovigilance specialist, and one methodologist/biostatistician. Every 400 inclusions, the DSMB reviews safety issues as the study progresses. The DSMB makes recommendations to the sponsor about the continuation, modification, or termination of the research. The recommendations that the DSMB can make are:
To continue the research with no modificationsTo continue the research with a modification to the protocol or the monitoring of subjectsTo temporarily halt inclusionsTo permanently terminate the research in light of severe adverse reactions.

The sponsor can stop trial recruitment on the advice of the DSMB in case of safety concerns.

The Scientific Committee, composed of [name] (M.D.), [name] (M.D, Ph.D.), and [name] (Ph.D) approves the main study protocol and any amendments to monitor and supervise the trial concerning its primary and secondary objectives, to review relevant information from additional sources, to consider the recommendations of the DSMB, and to resolve issues raised by the trial coordinating centers.

[name], as coordinating investigator, is responsible for the governance of the study with the Scientific Committee, the Study Sponsor, and the DSMB.

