### Follow-up data

Most of the data are collected during the first 10 min after induction of anesthesia. As the anesthetic procedure progresses, the data collection sheet is completed in the recovery room and attached to the medical record. Data are also reported in a centralized electronic case report form. The duration of patient follow-up is 7 days. In the event of earlier discharge from the hospital, patients are considered free from complications for the days out of the hospital.

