For secondary endpoints, the two groups will be compared with the use of logistic regression models for binary data (postoperative pneumonia, postoperative respiratory distress), with the use of linear regression models for continuous data (heart rate, systolic blood pressure) and with the use of Poisson regression models for count data (number of episodes of allergic manifestation, number of episodes of desaturation). All analyses will be adjusted for stratification factors and centers as random effect.

Continuous variables will be presented as mean and S.D.s (as median and quartiles, otherwise). Categorical data will be presented as exact numbers and percentages.

The DSMB will periodically conduct safety analyses, as described in the “Study oversight” section.

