## Trial status

Protocol version number: Version 3.0, 03-08-2020.

Protocol date: July 4, 2019

Recruitment start date: October 9, 2019

Planned recruitment end date: October 2021

The trial has already achieved many milestones. Sponsorship has been agreed: the trial is sponsored by the French ministry of health. Insurance for non-negligent harm has been provided by the University Hospital of Nantes (CHU Nantes, France). Research ethics committee approval was obtained in July 2019. It is registered with the American registry of trials (https://clinicaltrials.gov/ NCT03960801). Inclusions started on October 9, 2019. Due to the pandemic of COVID-19 pneumonia, the study has been suspended from March 20, 2020, to May 4, 2020, after the inclusion of 340 patients and before the first DSMB meeting. The recruitment process was resumed but we remain vigilant regarding the epidemiological evolution of COVID-19 pandemic.

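### Sites have 7 days to report any serious adverse event to the sponsor, with no shorter limit for fatal or life-threatening events at induction

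*Protocol article*

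**What the plan says.** The reporting rule is in the Study oversight section: "Serious adverse events and unexpected related or possibly related severe events are reported to the sponsor within 7 days". The article does not say whether the 7 days run from the event or from the investigator's awareness of it. Study endpoints defines serious adverse events as grades 3 (severe), 4 (life-threatening) and 5 (lethal) and has them recorded on day 1 and day 7. The one limit therefore covers all three grades.

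The same Study oversight section describes the central safety review: "Every 400 inclusions, the DSMB reviews safety issues as the study progresses". It adds: "The sponsor can stop trial recruitment on the advice of the DSMB in case of safety concerns". The analysis section refers back to this arrangement: "The DSMB will periodically conduct safety analyses, as described in the “Study oversight” section".

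Follow-up data states: "The duration of patient follow-up is 7 days". Under Procedures, the study drug is one intravenous bolus given straight after the hypnotic. Under Study endpoints, the major complications, including aspiration, cardiac arrest and grade III or IV anaphylaxis, are counted over the first 10 minutes after induction.

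**The concern.** The limit is as long as the patient's entire follow-up, while the major complications that the trial names occur within minutes of one injection. An event in the fifth minute is seen at once by the treating team and recorded on day 1, yet the site may hold it until that patient's follow-up ends.

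The treating site is not the place where a pattern would be seen. There are 15 units, and at the pre-suspension pace each includes about one patient a week. A cluster spread over several units becomes visible only centrally, once reports have arrived. The sponsor is the recipient of those reports and can stop recruitment on DSMB advice. What is at stake is how many more patients are randomised before the people who can act have the information. The effect sizes, the sample size and the primary analysis are not affected.

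**Working it through.** The article states no weekly accrual figure, so there is none to reproduce. The pace has to be derived from its dates and counts.

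**Inputs**
- Start (Trial status): "Inclusions started on October 9, 2019".
- Count and date before the pause (Trial status): "the study has been suspended from March 20, 2020, to May 4, 2020, after the inclusion of 340 patients and before the first DSMB meeting".
- Planned total 1150, allocated 1:1 (Sample size; Treatment allocation).
- Planned end of recruitment: October 2021, no day given (Trial status). I take 1 and 31 October as the two extremes.
- Number of units: 15 (Setting).
- Reporting limit: 7 days (Study oversight).

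**Formula.** Randomisations during a reporting lag = (patients ÷ days) × lag in days.

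**Days elapsed**
- 9 October 2019 to 20 March 2020: 22 + 30 + 31 + 31 + 29 + 20 = 163.
- 9 October 2019 to 1 or 31 October 2021: 723 or 753.
- Suspension, 20 March to 4 May 2020: 45. Without it, the planned period is 678 or 708.
- 4 May 2020 to 1 or 31 October 2021: 515 or 545, for the remaining 1150 − 340 = 810 patients.

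| Pace | Patients ÷ days | Per day | In 7 days |
|---|---|---|---|
| Observed before suspension | 340 ÷ 163 | 2.09 | 14.6 |
| Planned, whole period | 1150 ÷ 723 to 1150 ÷ 753 | 1.59 to 1.53 | 11.1 to 10.7 |
| Planned, suspension excluded | 1150 ÷ 678 to 1150 ÷ 708 | 1.70 to 1.62 | 11.9 to 11.4 |
| Needed after restart | 810 ÷ 515 to 810 ÷ 545 | 1.57 to 1.49 | 11.0 to 10.4 |

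The 7-day figure is therefore about 11 (10.4 to 11.9) at the planned or restart pace and about 15 at the observed pace. If arrivals are Poisson with mean 14.6, a single 7-day window would hold 8 to 23 patients with 95% probability.

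**Per arm.** With 1:1 allocation, half of these receive remifentanil: 14.6 ÷ 2 = 7.3 at the observed pace.

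**Per unit.** 14.6 ÷ 15 = 0.97 patients a week.

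**With a 24-hour limit.** The per-day column applies: 2.1 at the observed pace and 1.5 to 1.7 otherwise. The ceiling falls by 14.6 − 2.1 = 12.5 at the observed pace, and by 10.4 − 1.5 = 8.9 at the slowest pace.

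**Start of the clock.** For an event during induction, occurrence and awareness coincide, because the investigator's team is present. The missing clock start therefore does not change the figures here. It would matter for a death later in the week.

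**The DSMB interval.** It does not enter this calculation. The count depends on the reporting limit and the pace alone.

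**The case against.** **Seven days is a maximum.** Sites may report a death on the same day, and the faster pace comes from before the suspension. This stands: 11 to 15 is a ceiling.

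**The sponsor may learn of events another way.** Data go into a centralised online case-report form, and the sponsor's research assistants work closely with sites. This could shorten the delay in practice. However, the article gives no entry deadline for that form, so it does not replace a reporting limit.

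**These complications are anticipated.** Cardiac arrest and aspiration are components of the primary endpoint, and the design assumes that 20% of controls will not have an uncomplicated intubation. One event need not justify a halt, so further patients randomised are not patients harmed by delay. This stands, and it limits how strongly the point can be put. It does not explain why deaths and life-threatening events share one limit with grade 3 events.

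**The article is condensed.** The full protocol may hold more detail. But the article does not leave the limit out: it states one figure for all serious events.

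A reader might also infer three stronger points that the documents do not support:
- *That the DSMB can meet only at each 400th inclusion.* The article gives that interval and neither describes nor excludes an unscheduled review. The report that the pause came "after the inclusion of 340 patients and before the first DSMB meeting" is consistent with the interval and shows nothing about ad hoc meetings.
- *That the sponsor alone can halt recruitment.* The text says that the sponsor can do so on DSMB advice, not that nobody else can. The COVID-19 suspension shows that inclusions can stop without a DSMB meeting.
- *That Good Clinical Practice or an expedited-reporting deadline is breached.* The article commits to Good Clinical Practice but quotes no time limit from it and gives no deadline for the sponsor's own onward reporting.

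**Conclusion.** The point holds as a weakness in a stated rule. A single 7-day limit for all serious events, fatal and life-threatening ones included, is badly matched to a one-bolus exposure whose named complications fall within 10 minutes and whose serious events are already recorded on day 1. If a site uses the whole limit, up to about 11 (planned pace) to 15 (pre-suspension pace) further patients can be randomised before the sponsor need know of a death or cardiac arrest at induction, against about 2 with a 24-hour limit.

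The size rests on three assumptions: the report arrives on the last permitted day, no other route informs the sponsor sooner, and recruitment runs at one of the paces derived from Trial status. The finding does not depend on how often the DSMB meets, or on any reporting standard outside the article.

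**What to change.** Amend the reporting sentence in Study oversight in three ways:

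1. Serious adverse events, or at least those that are fatal, life-threatening, or unexpected and related, are reported to the sponsor without delay and no later than 24 hours after the investigator becomes aware. This also settles when the clock starts. Grades 4 and 5, already defined under Study endpoints, can mark the fatal and life-threatening tier.
2. The sponsor forwards fatal and unexpected related events to the DSMB chair on receipt.
3. The reviews at every 400 inclusions stay as they are.

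If the full protocol already has a shorter limit, only the article's sentence needs correcting.

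The cost is amendment wording, a letter to the 15 units and slightly faster paperwork for sites. The treatments, sample size, endpoints and analysis do not change.

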### Roles of the sponsor and the funder

The sponsor and of the funder had no role in the design or conduct of the study, the data analysis, the writing of the manuscript, or in the decision to submit the manuscript.

### Sample size

The proportion of successful tracheal intubation without any major complications is the primary outcome. In previous studies, the proportion of rapid sequence induction of general anesthesia with a rapid-onset paralytic agent without major complications ranged between 70 and 92%, depending on the studies and definitions [19–21]. It is also recommended to set non-inferiority margins lower than a 10% relative difference between the intervention and control groups [22]. Assuming an 80% rate of tracheal intubation without major complication in the rapid-onset paralytic agent group, and given the potential benefit of avoiding the use of rapid paralytic agents, we deemed it medically acceptable to set the non-inferiority margin to an absolute difference of 7% (8.75% relative difference). We thus calculated that a total of 1150 patients (575 patients per group) was needed to demonstrate the non-inferiority of the intervention with a statistical power of 80% an alpha risk of 2.5.

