### Treatment allocation

Randomization was performed through a secure web-based randomization system. The randomization list was generated by a statistician, not involved in determining the eligibility or the assessment of outcomes. The sequences were generated using the PROC PLAN procedure from SAS, version 9.4 (SAS Institute), and the statistician was the only one who knows size of the randomization blocks. Patients are randomized to the remifentanil (intervention group) or the rapid-onset paralytic agent (control group) in fixed blocks, in a 1/1 ratio, with stratification based on the type of laryngoscopy (direct vs. indirect video-laryngoscope, which is a risk factor of successful intubation at the first attempt) and on digestive occlusive syndrome (yes or no, which is a significant risk of gastric inhalation) (Fig. 1).

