### Pre-planned primary analysis

The statistical analysis will be carried out under the current recommendations for non-inferiority trial analysis [23].

The analysis of the primary outcome will be undertaken on the intention to treat principle including all randomized patients, and under the “per-protocol” principle, including all randomly assigned patients except those who withdrew consent for the use of all trial data, those who did not meet the inclusion criteria, those who did not receive the allocated study treatment, and those without data for the primary outcome [22, 23]. To comply with international recommendations on non-inferiority trials [24], the analysis based on the intention-to-treat principle and the data set for the per-protocol analysis will have equal importance to lead similar to a robust interpretation.

For the primary endpoint (proportion of successful tracheal intubation without major complications), the proportion difference between the two groups and the two-sided 95% confidence interval will be estimated. Under our assumptions, the remifentanil group will be considered non-inferior if the upper limit of the two-sided 95% confidence interval of absolute proportion difference does not exceed 7% (non-inferiority margin). The confidence interval will be estimated by a logistic model considering stratification on the existence or not of an occlusive syndrome and the type of equipment used for intubation. As the primary endpoint is identified within 10 min of anesthetic induction and death is included in the endpoint, a small amount of missing data will be expected. Multiple imputations methods based on demographic criteria and available data will be used in case of missing data. If non-inferiority is shown for the primary endpoint (on “intention-to-treat” and “per-protocol” populations), a superiority test will be assessed.

Preplanned subgroup analyses will be carried out on the primary outcome, following the same methodology:
Randomization stratum
*Type of equipment used for intubation (Macintosh laryngoscope vs. video laryngoscope).*Primary risk factor for pulmonary aspiration of gastric contents (occlusive syndrome vs. other causes)Age groups (18–40 years; 40–60 years; 60–80 years)Mallampati score (I and II vs. III and IV)Standard of care (urgent or non-urgent)Body mass index greater than 30 kg/m^2^ (yes vs. no)ASA Score (1–2 vs. 3–4)Choice of propofol as hypnotic (propofol vs. others)

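### The 1150 patients match a formula for detecting 80% versus 73%, not the planned non-inferiority test, for which 1150 give about 84% power if both true rates are 80%

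*Protocol article*

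**What the plan says.** The Sample size section sets out the inputs. For the control rate it says: "Assuming an 80% rate of tracheal intubation without major complication in the rapid-onset paralytic agent group". The authors considered it medically acceptable to "set the non-inferiority margin to an absolute difference of 7% (8.75% relative difference"). It then concludes: "We thus calculated that a total of 1150 patients (575 patients per group) was needed to demonstrate the non-inferiority of the intervention". The error rates attached to that number are 80% power and an alpha of 2.5. The section names no formula, no assumed success rate under remifentanil and no allowance for patients who cannot be evaluated.

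The Pre-planned primary analysis section defines the test. Non-inferiority is declared if the "upper limit of the two-sided 95% confidence interval of absolute proportion difference does not exceed 7" percent. Comparing one limit of a two-sided 95% interval with the margin is a one-sided test at 2.5%, so the alpha of 2.5 in the Sample size section reads as one-sided 2.5%. The same section says that the intention-to-treat and per-protocol analyses "will have equal importance to lead similar to a robust interpretation", and it requires non-inferiority in both before superiority is tested. The Treatment allocation section gives allocation "in fixed blocks, in a 1/1 ratio".

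**The concern.** The usual way to size a non-inferiority trial is to assume that the two treatments truly perform alike and to ask how many patients are needed for the confidence limit to clear the margin. With the article's own inputs this gives a smaller number than 1150. So either the number or the power beside it belongs to another calculation.

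Two things are at stake. The first is the power statement, which the results paper is likely to repeat. The second is the per-protocol analysis, which carries equal weight and leaves out patients who did not receive the allocated treatment, did not meet the inclusion criteria, lack primary outcome data or withdrew consent. How much power is left after such exclusions depends on what 575 per group really provides for the non-inferiority test, and the paragraph does not tell the reader.

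**Working it through.** **Inputs.** Control success 0.80, margin 0.07, power 80% (Sample size); one-sided alpha 0.025 (Sample size, with the confidence-interval rule in Pre-planned primary analysis); 1:1 allocation (Treatment allocation). Normal quantiles: 1.960 for alpha and 0.8416 for power; (1.960 + 0.8416)² = 7.849.

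**Step 1: reproduce 575.** Take 0.80 and 0.80 − 0.07 = 0.73 as the two true rates and use the pooled formula for detecting a difference.

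- Mean rate = (0.80 + 0.73)/2 = 0.765
- Pooled term = √(2 × 0.765 × 0.235) = √0.35955 = 0.5996
- Unpooled term = √(0.80 × 0.20 + 0.73 × 0.27) = √0.3571 = 0.5976
- n = (1.960 × 0.5996 + 0.8416 × 0.5976)² / 0.07² = (1.1752 + 0.5029)² / 0.0049 = 574.75

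This rounds up to 575 per group, or 1150 in total, the stated figure to the patient. The unpooled form gives nearly the same: 7.849 × 0.3571 / 0.0049 = 572.0, or 573 per group (1146).

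**Step 2: what that formula is for.** It gives 80% power to find a difference when remifentanil truly succeeds in 73%. In the planned test, 73% is the margin itself. At a true 73% against 80%, the expected difference equals the margin, and the chance of declaring non-inferiority is 2.5%, not 80%.

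**Step 3: the non-inferiority calculation, both true rates 0.80.**

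- n = 7.849 × (2 × 0.80 × 0.20) / 0.07² = 7.849 × 0.32 / 0.0049 = 512.6, so 513 per group and 1026 in total
- Power at 575 per group: standard error = √(0.32/575) = 0.02359; 0.07/0.02359 − 1.960 = 1.007; power = 84.3%

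**Step 4: other non-inferiority variants, same inputs.**

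| Method | Per group |
|---|---|
| Unpooled, equal rates | 513 |
| Farrington–Manning score | 516 |
| Continuity-corrected | 541 |
| Null variance at 80%/73% for the alpha term | 554 |
| Stated | 575 |

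None of these four reaches 575.

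**Step 5: room for exclusions.** 1 − 1026/1150 = 10.8%. With equal rates of 80%, power stays at 80% until about 10.8% are excluded. At 15% (an assumed figure), 489 per group remain and power is 78%.

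**Step 6: dependence on the unstated remifentanil rate.** At 575 per group, control 80%:

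| True remifentanil rate | Power |
|---|---|
| 80.0% | 84.3% |
| 79.6% | 79.6% |
| 79.0% | 71% |

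**The case against.** The strongest reply is that the number can be traced. Every input behind 575 stands in the article, and a recognised formula returns it exactly. This is correct, and it rules out two readings that a reader might be drawn to.

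- A reader might infer that 1150 does not follow from the stated inputs at all. It does, through the pooled formula for 80% versus 73%. What fails is the link between that formula and the test in the primary analysis.
- A reader might infer that the authors started from 1026 and silently added about 11% for losses. The article does not say so, and an exact match without any allowance makes it the less likely origin. A round 10% allowance would give 513/0.9 = 570 per group, not 575.

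It can also be said that the 84% assumes a remifentanil rate of 80% that the article does not state, and that a condensed article may leave such details to the full protocol. The first part stands: 84% is conditional, as the last table above shows. The second part does not remove the point. The criticism is not that a detail is absent, but that the article pairs 1150 with 80% power for demonstrating non-inferiority, and that this pairing belongs to another hypothesis.

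Finally, the effect is in the safe direction. With equal rates the trial has more patients than the usual calculation asks for, and the article expects little missing data for an endpoint settled within 10 minutes. This limits the weight of the point, and the conclusion takes it into account.

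**Conclusion.** The point holds in this form: 575 per group is the result of a difference-detection formula for 80% versus 73%, while the planned test is non-inferiority with a 7-point margin. Under equal true rates of 80%, that test needs 513 per group (1026), and the planned 575 give 84.3% power. The excess is 1150/1026 − 1 = 12%.

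That the authors used this formula is an inference from an exact numerical match, since the article names no method. The 513 and 84.3% rest on a true remifentanil rate of 80%; at 79% power is about 71%.

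A reader might conclude that the trial is underpowered or that enrolment must change. Neither follows: under equal rates the discrepancy is conservative. The article also cites control rates from 70 to 92%, and with equal rates in both groups power at 575 would run from 74% to 99% over that range. This shows sensitivity to an assumption and is not an error in the plan.

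**What to change.** Keep 1150 and restate the paragraph for the test that will be done, for example:

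> Assuming 80% success in both groups, a 7-point margin and one-sided alpha of 2.5%, 513 evaluable patients per group give 80% power. The planned 575 per group give about 84% power if all are evaluable, and keep 80% with up to about 10.8% excluded from the per-protocol set.

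If the authors planned on a remifentanil rate other than 80%, they should state that rate and recompute these figures. The surplus over 513 should not be described as a loss allowance planned from the start, because the article does not say that it was. The cost is a text correction, with no change to enrolment, margin or analysis.
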